# The effect of robot-assisted versus standard training on motor function following subacute rehabilitation after ischemic stroke – protocol for a randomised controlled trial nested in a prospective cohort (RoboRehab)

**DOI:** 10.1186/s12883-024-03734-9

**Published:** 2024-07-04

**Keywords:** Stroke, Body weight unloading, Gait training, Functional training, Neurorehabilitation, Motor learning, Neuroplasticity

## Abstract

**Background:**

Body weight unloaded treadmill training has shown limited efficacy in further improving functional capacity after subacute rehabilitation of ischemic stroke patients. Dynamic robot assisted bodyweight unloading is a novel technology that may provide superior training stimuli and continued functional improvements in individuals with residual impairments in the chronic phase after the ischemic insult. The aim of the present study is to investigate the effect of dynamic robot-assisted versus standard training, initiated 6 months post-stroke, on motor function, physical function, fatigue, and quality of life in stroke-affected individuals still suffering from moderate-to-severe disabilities after subacute rehabilitation.

**Methods:**

Stroke-affected individuals with moderate to severe disabilities will be recruited into a prospective cohort with measurements at 3-, 6-, 12- and 18-months post-stroke. A randomised controlled trial (RCT) will be nested in the prospective cohort with measurements pre-intervention (Pre), post-intervention (Post) and at follow-up 6 months following post-intervention testing. The present RCT will be conducted as a multicentre parallel-group superiority of intervention study with assessor-blinding and a stratified block randomisation design. Following pre-intervention testing, participants in the RCT study will be randomised into robot-assisted training (intervention) or standard training (active control). Participants in both groups will train 1:1 with a physiotherapist two times a week for 6 months (groups are matched for time allocated to training). The primary outcome is the between-group difference in change score of Fugl-Meyer Lower Extremity Assessment from pre-post intervention on the intention-to-treat population. A per-protocol analysis will be conducted analysing the differences in change scores of the participants demonstrating acceptable adherence. A priori sample size calculation allowing the detection of the minimally clinically important between-group difference of 6 points in the primary outcome (standard deviation 6 point, α = 5% and β = 80%) resulted in 34 study participants. Allowing for dropout the study will include 40 participants in total.

**Discussion:**

For stroke-affected individuals still suffering from moderate to severe disabilities following subacute standard rehabilitation, training interventions based on dynamic robot-assisted body weight unloading may facilitate an appropriate intensity, volume and task-specificity in training leading to superior functional recovery compared to training without the use of body weight unloading.

**Trial Registration:**

ClinicalTrials.gov. NCT06273475.

Trial status: Recruiting.

Trial identifier: NCT06273475.

Registry name: ClinicalTrials.gov.

Date of registration on ClinicalTrials.gov: 22/02/2024.

**Supplementary Information:**

The online version contains supplementary material available at 10.1186/s12883-024-03734-9.

## Background

Ischemic stroke is an acute focal injury to the central nervous system (CNS) caused by a disturbance in the blood circulation of the brain leading to cerebral infarction. The increased neuroplasticity observed in the initial weeks after ischemic stroke has been marked as a critical period for subacute rehabilitation [1, 2]. However, in the chronic phase, 6 months post-stroke, individuals may display residual impairments in motor, muscle, physical, and cognitive function in addition to depression, mental and exertional fatigue, reduced aerobic capacity, and reduced quality of life [3–8]. Several rehabilitation strategies have been employed for stroke-affected individuals in the chronic phase [9, 10], however, most studies have included individuals with mild/moderate disability and not severely impaired individuals [4, 9]. Hence, intervention studies are needed to highlight the efficacy of chronic-phase stroke-rehabilitation in individuals with moderate to severe disability despite subacute rehabilitation.

Body weight unloading (BWU) has been suggested as a training method for people with neurological disorders who suffer from severe limitations in walking ability [11]. BWU is the application of a vertical upwards force on the body centre of mass, which reduces the kinetic requirements of locomotion [12]. BWU may allow severely impaired stroke-affected individuals, who are unable to support their own body weight against gravity, to achieve an appropriate and adjustable intensity and volume for recovery of physical function. Furthermore, this method alleviates the therapist of supporting the individual against gravity during weightbearing exercises enabling a more dedicated focus on the quality of the exercise [11, 12]. However, there is limited evidence to support the efficacy of BWU in chronic stroke rehabilitation [9, 10]. Motor learning is a central part of neurorehabilitation interventions [12, 13] due to the associated neural adaptations [14–17]. Basic science studies within motor learning has led to important principles for neurorehabilitation such as active mental engagement, task-specificity, appropriate intensity, volume, and assistance and continuously providing variable and goal-oriented challenges [15, 18–20]. However, earlier studies on BWU exhibit differences, particularly within intensity and volume of training [9]. Furthermore, studies have differed in choice of control group (BWU gait training versus overground gait training, conventional physical therapy, or no intervention), and inclusion criteria (lack of studies on non-ambulatory individuals) [9]. Taken together, these factors may have contributed to the limited efficacy shown for BWU in chronic stroke rehabilitation.

In the present study, robot-based BWU technology yielding a dynamic type of unloading [21] will be employed. The use of this technology has previously been shown to be feasible and safe in healthy adults [22]. Additionally, this dynamic BWU is not limited to facilitating treadmill gait training but can also be used to facilitate overground walking, stair negotiation, and functional task-specific training such as sit-to-stand, squat, and lunges. Dynamic unloading provides a modulated continuously accommodating force that is highly responsive to the movements of the unloaded individual, and this may be superior to no BWU by yielding a more appropriate intensity and volume in training. Furthermore, the presently employed dynamic BWU has been shown to preserve biomechanical gait patterns of healthy individuals [23] and it may be that the current type of dynamic BWU facilitates greater task-specificity in training compared to training without BWU.

The aim of the present study is to investigate the effect of a 6-month robot-assisted dynamic BWU intervention versus standard training, initiated 6–18 months post-stroke, on motor function, physical function, fatigue, and quality of life in a moderately-to-severely impaired stroke population. The main hypothesis of the study is that robot-assisted dynamic BWU training has a superior effect in comparison to standard training on motor function (Fugl-Meyer Lower Extremity Assessment; primary outcome), physical function, fatigue, and quality of life in stroke-affected individuals, still suffering from moderate to severe disabilities after standard subacute rehabilitation.

## Methods

### Experimental Protocol

#### Study design

The present project comprises a randomised controlled trial (RCT) nested in a prospective cohort. The RCT will be conducted as a multicentre parallel-group superiority of intervention study with assessor-blinding. Stroke-affected individuals will be included in a prospective cohort at 3 months post-stroke until 18 months post-stroke with the aim of investigating recovery according to standard rehabilitation i.e. “usual care”. Eligible individuals (those with persistent moderate to severe disability) will be recruited to the RCT-study from the prospective cohort and/or municipal rehabilitation at 6–18 months post-stroke. Individuals not eligible for and/or not interested in the RCT-study will continue their participation in the prospective cohort or municipal rehabilitation.

The present protocol was registered at ClinicalTrials.gov (NCT ID: NCT06273475). The primary and certain secondary outcome measurements are based upon recommendation from a core outcome set of measurements [24]. The current protocol follows the SPIRIT recommendations (Standard Protocol Items: Recommendations for Interventional Trails) (see Additional file 1 for the SPIRIT Checklist and Fig. 1 for the SPIRIT Fig. [25]) for the minimum content of a controlled trial protocol, and findings will be reported in accordance with the CONSORT statement [26]. Prior to inclusion, pilot experiments will be conducted on 4–6 stroke-affected individuals.

**Fig. 1 Fig1:**
[figure not shown]
SPIRIT Figure. Template of content for the schedule of enrolment interventions, and assessments. Spirit Figure for the randomised controlled trial. Abbreviations: FM-LE: Fugl-Meyer Lower Extremity Assessment of Motor Function; BI: Barthel Index; BBS: Berg Balance Scale; FAC: Functional Ambulation Category; MAS: Modified Ashworth Scale; HGS: Hand-grip strength; 10-MWT: 10-meter walking test; MS: Muscle Strength; mSTS: modified sit-to-stand; mRS: modified Rankin Scale; IPAQ: International Physical Activity Questionnaire; EQ-5D: Health related quality of life; FSS-7: Fatigue severity scale 7; NF-L: Neurofilament light chain; GFAP: Glial Fibrillary Acidic Protein; PMBCs: Peripheral Blood Mononuclear Cells

#### Randomisation

The present RCT will use a stratified block randomisation design. Randomisation will be performed internet-based using REDCap Randomise, allocated 1:1. Allocation sequence will be stratified according to global disability (modified Rankin Scale (mRS) score 3, 4 and 5) in blocks of 2 and 4. Stroke-affected individuals will be randomised to robot-assisted dynamic BWU training (INT) or standard training (CON) following pre-intervention testing. The allocation sequence is provided by a data manager with no clinical involvement in the trial, and it is concealed in a password-protected computer file only accessible to the data manager. Participants will be randomised to the intervention group or the active control group by a member of the research team not involved in outcome assessment or statistical analysis.

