#### Trial sites

Two trial centres are established for the present project (Odense and Copenhagen) to ensure the study meets the target sample size with an adequate flow of participants through the study. The trial centre in Odense is affiliated with Odense University Hospital, and the attached training facility is located at the Department of Sport Science and Clinical Biomechanics (University of Southern Denmark). The trial centre in Copenhagen is affiliated with Herlev and Gentofte Hospital and ‘Rigshospitalet’, and the attached training facility is located at the outpatient clinic at “Bodil Eskesen Centret”. Testing and training will run parallel in Odense and Copenhagen with two different training teams. Experiences/knowledge regarding individualisation/progressions will be shared between trial sites to ensure standardisation of intervention delivery. A technician working on the research project will be responsible for the functionality of the robots.

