### Statistical Analysis

#### Primary Analysis

An assessor-blinded intention-to-treat (ITT) analysis will be performed on primary and secondary outcome measures (Primary Analysis). The ITT analysis will employ a two-way analysis of variance (ANOVA) to analyse between-group differences in change-scores from pre- to post-intervention. No interim analysis will be performed. Full analysis data sets will be created with multiple imputation as part of a sensitivity analysis to examine the robustness of the primary analysis.

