#### Sample size calculation

A priori two-sided sample size calculation for two independent groups was performed and resulted in a required sample size of 34 study participants in total. This was based on detecting a minimally clinically important between-group difference (MCID) of 6 points on the FM-LE scale [55] and a standard deviation of 6 points [28, 30, 55] at an α level of 5% and with a statistical power of 80%. Allowing for dropout the aim is to include 40 participants in total.

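### The stated ANOVA commits to neither the mRS stratum used in randomisation nor centre; if mRS predicts FM-LE change, leaving it out makes the primary test conservative and costs power

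*Protocol article*

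**What the plan says.** All references are to the protocol article.

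- **Randomisation:** "Allocation sequence will be stratified according to global disability (modified Rankin Scale (mRS) score 3, 4 and 5) in blocks of 2 and 4". Allocation is 1:1, and centre is not listed as a stratum.
- **Trial sites:** there are two centres. "Testing and training will run parallel in Odense and Copenhagen with two different training teams".
- **Primary Analysis:** the intention-to-treat analysis of primary and secondary outcomes uses a two-way ANOVA "to analyse between-group differences in change-scores from pre- to post-intervention". Neither of its two factors is listed.
- **Secondary analyses:** the per-protocol comparison is an ANOVA on change scores, again with no factor beyond group named.
- **Sample size calculation:** "A priori two-sided sample size calculation for two independent groups was performed". It targets a "minimally clinically important between-group difference (MCID) of 6 points on the FM-LE scale" with "a standard deviation of 6 points", and it "resulted in a required sample size of 34 study participants in total". The recruitment aim is 40.
- **Statistical analysis plan:** a separate plan is to be made public before analysis. It is not at hand.

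**The concern.** Blocking within mRS strata keeps the arms close to balanced on mRS. Differences in outcome between mRS levels then contribute almost nothing to the sampling error of the treatment difference. A model without the stratum still counts those differences as residual variation. If mRS is related to change in FM-LE, the reported standard error exceeds the true one, the confidence interval is too wide, and the test rejects less often than its nominal 5%. The trial would have paid for the balance and not collected the precision.

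Centre is a different case. Therapists, facilities and probably assessors differ between the two sites, and nothing in the allocation balances the arms by site. A chance excess of one arm at one site would mix any site difference into that trial's estimate, and no stated term removes it.

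The wording two-way does not settle the matter. A change score has already used up time, so some second factor besides group is implied, but the text does not say which. If a group-by-time ANOVA on the raw scores is meant, its interaction test is equivalent to an unadjusted comparison of change scores and contains neither stratum nor centre.

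**Working it through.** **1. The plan's own figure.** Inputs from Sample size calculation: difference 6, SD 6, two-sided α 5%, power 80%. The two-sample t-based calculation gives 16.71, hence 17 per arm and 34 in total, with power 80.7%. The stated figure reproduces. With 20 per arm, power is 86.9%. The sample size is not at fault.

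**2. Closed-form size of the mRS effect.** Let R² be the share of the variance of FM-LE change explained by mRS (assumed; not in the documents). With 17 per arm and perfect balance within strata:

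- Standard error reported without the stratum: 6 × √(2/17) = 2.06.
- True spread of the estimate: 6 × √((1 − R²) × 2/17).
- Approximate type I error: 2Φ(−1.96/√(1 − R²)).

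| R² | Reported SE | True spread | Ratio | Approx. type I |
|---|---|---|---|---|
| 0 | 2.06 | 2.06 | 1.00 | 5.0% |
| 0.1 | 2.06 | 1.95 | 1.05 | 3.9% |
| 0.2 | 2.06 | 1.84 | 1.12 | 2.8% |
| 0.3 | 2.06 | 1.72 | 1.20 | 1.9% |

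Incomplete blocks leave some imbalance, so the real trial would sit slightly nearer 5% than this limit.

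**3. Simulation.** This used permuted blocks of 2 and 4 within mRS strata, total SD 6, an assumed mRS mix of 40/40/20% and an assumed 50:50 centre split. There were 4,000 trials per setting. Power is for the planned 6 points at N = 34:

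| R² (mRS) | Group alone | Group + mRS | Group + mRS + centre |
|---|---|---|---|
| 0 | 80.5% | 80.3% | 78.6% |
| 0.1 | 81.1% | 83.6% | 82.6% |
| 0.2 | 82.9% | 88.5% | 87.7% |
| 0.3 | 84.6% | 92.0% | 90.8% |

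At R² = 0.2 the mean reported standard error is 2.05 for group alone, against 1.83 with mRS and 1.87 with mRS and centre.

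Type I error for group alone was 4.3%, 3.4%, 2.5% and 2.6% across the four rows. A second simulation gave about 5%, 3.6%, 2.9% and 2.5%. The Monte Carlo standard error at 5% with 4,000 trials is √(0.05 × 0.95/4000) = 0.34 percentage points, so the two sets are compatible. The adjusted model stayed between 4.2% and 5.4%.

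At N = 40, power for group alone against group + mRS + centre is 87.0% against 85.9% at R² = 0, and 88.3% against 92.2% at R² = 0.2.

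**4. Centre.** Assume 20 per arm and 20 per centre. The number of one arm at one centre is then hypergeometric(40, 20, 20).

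- P(12:8 or worse) = 0.343, and P(13:7 or worse) = 0.113.
- In the blocked simulation, where the centre split varies by chance, a gap of 20 percentage points or more in centre share occurred in 22-25% of trials.
- A 12:8 split is 60% against 40%, a gap of 0.20. If the centres differ by an assumed 1 to 3 points in mean change, the estimate moves by 0.20 × 1 = 0.2 to 0.20 × 3 = 0.6 points, against a target of 6.
- With centre explaining an assumed 10% of variance and omitted, type I error is 4.7% at N = 34 and 5.0% at N = 40. It is therefore not inflated. At N = 34, power is 80.7% for group alone against 82.4% with mRS and centre in the model.

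**5. Cost of the terms.** mRS uses two degrees of freedom and centre one. Residual degrees of freedom at N = 34 go from 34 − 2 = 32 to 29. The largest power loss at N = 34 is 80.5 − 78.6 = 1.9 points, when neither factor is prognostic.

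**The case against.** The strongest reply is that the article excludes nothing. The second ANOVA factor is unnamed and could be mRS stratum or centre, and a separate analysis plan is the usual place for model terms. This stands against a reading that a reader might infer, namely that both factors are left out of the analysis. The text does not say so. What survives is narrower. The article states its primary method, and as stated the method cannot be carried out from the text and does not commit to the one factor that the randomisation was built on.

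A second reply is that too wide is conditional. mRS must predict the change in FM-LE, not merely its level, and the documents give no figure. That stands too. At R² = 0 nothing is lost by omission and adjustment costs 1 to 2 power points. The direction is also conservative, so a positive result would not be undermined, and at N = 40 the planned 80% is exceeded either way. The argument applies only to mRS, because centre was not balanced by design.

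Third, a reader might infer that leaving centre out of the strata biases the trial. It does not. Averaged over randomisations the shift is zero, and type I error stays near 5%. The protocol also takes steps to keep the sites comparable: an external consultant physiotherapist, training in delivery, sharing of experience between sites, a standard operating procedure for testing, and blinded raters. Crossing three mRS levels with two centres would give six cells of about seven participants each (40/6 = 6.7), so leaving centre out of the strata is defensible.

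**Conclusion.** The point holds as a missing commitment in a stated method. The primary ANOVA does not identify its second factor, and neither it nor the per-protocol ANOVA commits to mRS stratum or centre. If mRS is prognostic for change and omitted, the test is conservative: at N = 34, type I error falls from about 5% to between 3.6% and 2.5% as R² goes from 0.1 to 0.3, and about 5 power points are lost at R² = 0.2. These sizes rest on assumed R², mRS mix and centre split.

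The documents do not support saying that the interval will be too wide, that false positives rise, or that centre introduces systematic bias. Centre is a matter of precision and credibility in the one trial realised. The weight is moderate: the stated sample size is sound and the error is on the safe side, but the remedy is nearly free.

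**What to change.** State the factors of the primary ANOVA by name. Prespecify treatment group and mRS stratum (3, 4, 5) as fixed terms, with centre (Odense, Copenhagen) as a further fixed term. Use the same terms for the secondary outcomes and the per-protocol analysis. Put this in the analysis plan before unblinding, with a rule for pooling an mRS stratum that turns out to be empty or represented in one arm only.

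The cost is wording, three degrees of freedom, and at most about 2 power points if neither factor matters. No extra participants are needed, and the randomisation strata need not change.

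If the second factor was always meant to be mRS stratum or centre, saying so and adding the other term is enough.

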#### Blinding

The investigator ([name]) is blinded towards group allocation, blinded during the primary analysis (c.f. *Statistical Analysis*), and is not involved in outcome assessment. Randomisation is performed after pre-intervention testing, and participants will be asked to refrain from revealing group allocation at post-intervention testing in order to ensure blinding of outcome assessors. The raters conducting pre- and post-intervention testing are blinded towards group allocation. Blinding of study participants and physiotherapists will not be possible due to the nature of the intervention.

#### Inclusion and exclusion criteria

The inclusion criteria are as follows: 1) ischemic stroke, 2) > 3 months post-stroke at inclusion in the prospective cohort 2) chronic state at inclusion in the RCT (6–18 months post-stroke), 3) moderate to severe disability defined as having a mRS score of 3–5 and a Scandinavian Stroke Scale (SSS) leg motor function score of 0–4, 4) subacute rehabilitation should be terminated (subacute phase defined as up till 6 months post-stroke), and 5) approved by referring doctor.

Exclusion criteria are as follows: 1) severe fatigue making study completion improbable, 2) cognitive deficits impeding study participation, 3) inability to walk independently pre-stroke, 4) recurrence of cardiovascular/cerebrovascular accidents, 5) pre-existing neurological diseases or ongoing cancer treatment, 6) previously hospitalised due to stroke, transient ischemic attack (TIA), or subarachnoid haemorrhage (SAH), 7) refusing group allocation, and 8) concurrent participation in another trial potentially interacting with the present trial.

### Recruitment and informed consent

The recruitment and flow of study participants through the present project is highlighted in the patient flow-chart (*c.f. *Fig. 2).

**Fig. 2 Fig2:**
[figure not shown]
Flow-chart of the study. Abbreviations: PROMs: Patient-reported outcome measurements. Participants not eligible for/interested in RCT participation will continue participation in the prospective cohort

